#### Treatment effects at follow-up

In order to investigate consolidation of the treatment effects over time on both the primary outcome (psychological distress) and secondary outcomes (all secondary outcomes except objective sleep parameters) we will again perform linear mixed effect models with time (T1, T2, T3, T4), group (MBCT + TAU versus TAU) and Group*Time interaction, including the same parameters as mentioned above and controlling for baseline levels and stratification variables. Restricted maximum likelihood will be used as estimation method to handle missing data. Cohen’s *d* will be calculated by dividing the adjusted group difference between the means at T4 by the pooled standard deviation at T0.

We also aim to examine the effect of MBCT on recurrence of disease activity (flares). Therefore, we will perform a proportional hazards model (i.e. Cox regression analysis) to analyse the differences between MBCT + TAU and TAU alone in time to flare within the 12-months study period.

#### Moderation analyses

Moderation analyses will be performed by adding the interaction terms of potential moderators with group to above mentioned post-treatment and follow-up models. We will run these analyses for the effect of group on psychological distress (HADS) and positive mental health (MHC-SF) scores at post-treatment and their course during 12 months follow-up. Separate models will be run for each possible moderator and for both outcomes. The following moderators will be used: age, sex, level of education, IBD type, disease duration, type of IBD medication (aminosalicylates, immunosuppressants, biologicals (including small molecule therapy)), repetitive thinking, mindfulness, self-compassion, psychological distress (HADS) and positive mental health (MHC-SF).

#### Mediation analyses

In order to assess whether the measured effect on psychological distress at posttreatment can be (partially) explained by changes in mindfulness skills, self-compassion, repetitive negative thinking and sleep quality, we will perform mediation analysis following the recommendations by Preachers and Hayes [74] for multiple mediation models. Psychological distress scores at post-treatment will be controlled for its baseline levels in all mediation analyses. Standardised residualised change scores for all potential mediators will be calculated [75]. We will first estimate the indirect effect of the potential mediators using a univariate model. Next, the variables shown to have a mediating role in the univariate models will be entered into a multivariate model to assess their relative contributions. A nonparametric bootstrapping method will be used to assess the indirect effect based on 5000 bootstrapped samples using bias corrected and accelerated 95% confidence intervals as provided by Hayes [76] in the SPSS PROCESS macro version 4.1.

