### Statistical analysis

#### Sample size calculation

Based on the most recent meta-analysis of MBCT in IBD, we anticipate the effect size of the reduction of psychological distress to be Cohen’s *d* = 0.51 [17]. With an error probability of 0.05, 0.80 power and a 1:1 allocation ratio, the required total sample size is 98. To account for dropout, we looked at dropout rates in the two similar RCTs of MBIs in patients with IBD, which were 11.5% [18] and 44% [19], respectively. These rates were averaged, i.e. 28%. Using the formula N = n/(1-(z/100)), our corrected sample size is N = 136 (n = 68 per condition).

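### Mediators are screened on their single-mediator result before the joint model, so the joint-model indirect effects that are reported are biased, usually upward

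*Protocol article*

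**What the plan says.** The Mediation analyses section of the protocol article asks whether the effect on post-treatment distress can be explained, at least in part, by "changes in mindfulness skills, self-compassion, repetitive negative thinking and sleep quality". It proceeds in two steps.

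- Step 1: "We will first estimate the indirect effect of the potential mediators using a univariate model".
- Step 2: "the variables shown to have a mediating role in the univariate models will be entered into a multivariate model to assess their relative contributions".

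Inference on the indirect effects is "based on 5000 bootstrapped samples using bias corrected and accelerated 95% confidence intervals". On adjustment: "Psychological distress scores at post-treatment will be controlled for its baseline levels in all mediation analyses". The section says that it follows published recommendations "for multiple mediation models", but it states no model that contains all four candidates regardless of step 1. It gives no threshold for passing step 1 and no correction of the intervals for the selection.

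**The concern.** The candidates are few and named in advance, so nothing forces a screen. Screening and then estimating in the same data has two effects on the joint model.

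1. Selection. A mediator enters only if its estimated indirect effect was large relative to its error, so the estimates that get through are on average too large.
2. Omission. If a dropped mediator is correlated with the retained ones, part of its path to the outcome loads on them. Correlation is plausible here: under Mental health-related measures, the self-compassion scale itself contains a mindfulness scale, and the mindfulness and perseverative-thinking questionnaires cover neighbouring ground.

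The joint model is the one meant to show how much each mechanism contributes. A contribution calculated only among survivors does not answer that question for the four constructs named. The Discussion hopes that the mechanisms found can guide mindfulness interventions in other chronic illnesses, so the sizes reported will be used.

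**Working it through.** **Sample size available.** The article gives no figure for the mediation analysis, so the planned numbers set the range. The article states: "With an error probability of 0.05, 0.80 power and a 1:1 allocation ratio, the required total sample size is 98", for d = 0.51. Averaging the two dropout rates gives (11.5 + 44)/2 = 27.75%, rounded to 28%, and 98/(1 − 0.28) = 136.1, so 136 reproduces. The 98 reproduces with a one-sided t-test (a two-sided test needs 124). The article does not state the sidedness; that is a separate matter. I use 98 and 136.

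**Effect of omission, in closed form.** Write the mediators as Mj = aj·G + ej, with unit variance and common residual correlation ρ, and the outcome as Y = c·G + Σ bj·Mj + error. The indirect effect is aj·bj. If one mediator (coefficient b4) is dropped and k are kept, each kept coefficient becomes

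bj + b4·ρ/(1 + (k − 1)ρ).

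Take the assumed paths a = 0.5, 0.5, 0.5, 0.3, |b| = 0.3, 0.2, 0.3, 0.2 and ρ = 0.5, and drop the fourth. The added term is 0.2 × 0.5/(1 + 2 × 0.5) = 0.05.

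- First and third: 0.5 × 0.35 = 0.175, against a true 0.150.
- Second: 0.5 × 0.25 = 0.125, against a true 0.100.
- Shares over survivors: 0.175/0.475 = 0.37, 0.26 and 0.37. The true shares are 0.33, 0.22, 0.33 and 0.13.

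This is before any selection effect.

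**Both effects together, by simulation.** There were 3,000 trials per scenario. A mediator was kept if the 95% Monte Carlo interval for its single-mediator indirect effect excluded zero. This stands in for the BCa bootstrap, and baseline HADS was left out for simplicity. True indirect effects were 0.150/0.100/0.150/0.060. Table entries are mean absolute indirect effects.

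| N | ρ | All four entered | Screened, given survival | Ratio to truth | All four kept |
|---|---|---|---|---|---|
| 98 | 0.5 | 0.150/0.100/0.149/0.059 | 0.220/0.166/0.218/0.116 | 1.45 to 1.93 | 24% |
| 136 | 0.5 | 0.151/0.099/0.150/0.060 | 0.189/0.135/0.190/0.095 | 1.26 to 1.58 | 37% |
| 98 | 0 | 0.148/0.099/0.150/0.062 | 0.206/0.180/0.208/0.161 | 1.37 to 2.68 | 0.6% |
| 136 | 0 | 0.151/0.099/0.149/0.060 | 0.175/0.145/0.175/0.124 | 1.17 to 2.07 | 5% |

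At ρ = 0 omission does not bias the kept coefficients, so those ratios are selection alone. Median shares at N = 98 and ρ = 0.5 were 0.39/0.29/0.39/0.19 with the screen and 0.32/0.21/0.32/0.11 without it.

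**A mediator with no path of its own** (b = 0, a = 0.5, ρ = 0.5) passed the screen in 59% of trials at N = 98 and 79% at N = 136. It was then significant in the screened joint model in 7.7% and 7.0% of trials, against 3.6% and 3.8% with all four entered.

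**A mediator acting the other way** (true +0.075) averaged +0.025 at N = 98 and +0.054 at N = 136 when it survived, so it was understated.

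**Other assumptions.** With true effects 0.125/0.075/0.075/0.040, ρ = 0.5 and a joint-significance screen at 5%, the screened means at 98 were 0.171/0.115/0.116/0.070 (1.4 to 1.8 times truth), and 1.2 to 1.4 times at 136. A different set of paths with the same products gave 1.2 to 1.9 and 1.1 to 1.3. Further assumed paths gave about 1.4 to 3.0 at 98 and 1.2 to 2.2 at 136.

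**The case against.** A reader might infer that the screen spoils the ranking of mechanisms. The calculations do not support this. With true effects 0.125/0.075/0.075/0.040, ρ = 0.5 and two sets of paths, the truly largest mediator came first in 47% and 46% of trials at 98 with all four entered, and in 43% and 47% of trials with at least one survivor under the screen. At 136 the figures were 51% and 51% against 48% and 51%. Across all checks the difference stayed within about 6 points in either direction. Ranking is poor because the sample is small. Nor is ranking the stated aim: the section asks whether the effect is partly explained by the mediators, and step 1 addresses that for every candidate without selection.

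A reader might also infer that every surviving effect is too large. That does not hold for opposing mediators. Averaged over all trials with dropped mediators counted as zero, screened estimates can sit near the truth (0.115 to 0.128 for a true 0.125). But readers will see the estimates that survived, and for those the bias stands.

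The path sizes, the correlation and the screening rule are assumptions, and an article may leave the definition of passing to a fuller document. That limits what can be said about size. It does not remove the rule, which the article states outright.

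Finally, four constructs are not yet four variables. Sleep quality alone is measured by PSQI, ISI, EEG headband and wristband, and the mindfulness questionnaire has five facets. The fix must therefore fix one score for each construct.

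**Conclusion.** The point holds for the joint model. Given survival, its indirect effects are biased, usually upward, by a factor of about 1.2 to 3 at 98 to 136 participants. A few ratios were nearer 1.1, and the bias shrinks as power rises. A mediator acting in the opposite direction can be understated. Shares are distorted as well, because they are taken over survivors and a dropped correlated mediator's path is partly credited to the rest. The direction follows from the stated rule; the size rests on assumed paths, correlation and screen. The single-mediator estimates are unaffected if all four are reported, and the article does not say that they would be withheld. The primary HADS comparison is also unaffected. This is an improvement to a secondary, explanatory analysis.

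**What to change.** Enter all four pre-named constructs in the multiple-mediator model whatever the single-mediator results, with one named score for each construct. Report all four specific indirect effects with their bootstrap intervals, and present the single-mediator models as descriptive. In the simulations this model recovered the true effects closely.

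The cost is a change of plan wording and somewhat wider intervals, because the mediators are correlated. No extra data are needed. The change should be justified by unbiased effect sizes and a complete account of the four constructs, not by a better ranking, which it does not materially provide.

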#### Cost-effectiveness

The cost-effectiveness evaluation will be carried out from both a healthcare and societal perspective considering direct as well as indirect costs. Data on resource use (healthcare uptake) and productivity losses will be collected with the TiC-P. Total costs, measured with the TiC-P will be estimated using an incremental bottom-up micro-costing approach, where costs for each patient will be obtained by multiplying information on each element of service with standard costs, based on the Dutch guideline for costing research [67]. We will consider three types of costs: (1) intervention costs of offering MBCT; (2) costs related to healthcare uptake; and (3) costs stemming from productivity losses due to absenteeism. The recall period will be four weeks at baseline, and will consist of three months (the entire period between each follow-up assessment) at 3, 6, 9 and 12 months follow-up. Health related QoL data (based on EQ-5D) from baseline up till 12 months will be used to calculate QALYs using the trapezium rule. Overall mean and median costs and health related QoL will be compared across the conditions and where relevant, differences will be calculated inclusive of 95% confidence intervals. Incremental cost-effectiveness will be determined in terms of incremental costs per QALY gained. The Incremental cost-effectiveness ratio will be determined on the basis of incremental costs and effects of MBCT compared to TAU. Bootstrap simulations with 1.000 replications will be used to get uncertainty intervals in our economic evaluation, taking into account the correlations between costs and QALYs. In addition, a cost-effectiveness acceptability curve will be produced to show the probabilities that given a certain value for the cost-effectiveness threshold, either of the tested strategies is the cost-effective option. In case of missing data, we will use multiple imputation methods to estimate the missing values.

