### Intervention: MBCT

The MBCT program is based on the protocol published by Segal, Williams and Teasdale [14]. The program consists of eight weekly 2.5 hour sessions, a six hour silent day between session 6 and 7, and daily home practice of 45 minutes guided by audio files. Groups consist of eight to ten participants. Materials are adjusted to include IBD-related examples. The course is offered in the cities where patients are treated (Nijmegen, Arnhem and ‘s-Hertogenbosch) and taught by qualified teachers according to the advanced criteria of the Association of Mindfulness-Based Teachers in the Netherlands and Flanders [28]. These criteria include a minimum of 150 hours of education in MBSR/MBCT (entailing theoretical background, skills practice, supervision and reflection), a minimum of three years of personal meditation practice and attending retreats, and providing a minimum of two courses per two years. All mindfulness teachers participated in a kick-off meeting before the start of the trial, in which the trial-specific MBCT protocol was discussed. Peer supervision meetings are organised twice per MBCT course during the intervention phase of the trial. Teaching sessions are recorded and a random sample of sessions will be rated by two independent raters using the Mindfulness-Based Interventions: Teaching Assessment Criteria (MBI:TAC) [29]. Participation of the training can be discontinued on participant’s request at any time. If so, the participant is encouraged to complete further assessments of the study.

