The *Mindfulness Adherence Questionnaire* (MAQ) is a 12-item questionnaire about mindfulness practice [64]. The first 2 items measure formal practice in terms of frequency and average duration of practice. The remaining items measure the quality of formal practice. Items are scored on a 7-point Likert-scale. Higher subscale scores reflect higher practice quality for that respective practice type. Because a Dutch version of the questionnaire was not available yet, we translated and back-translated the original MAQ for the purpose of this study. The reliability of the English version has been shown to be adequate (Cronbach’s *α* = 0.79) [64].

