#### Cost-effectiveness

Cost-effectiveness is investigated using the *Trimbos and iMTA questionnaire for Costs associated with Psychiatric illness* (TiC-P) as a reliable and valid measure of healthcare utilization and productivity losses at work and in daily life [65, 66]. Unit cost estimates will be derived from the national manual for cost prices in the healthcare sector [67].

Health-related QoL, using the *EuroQol-5D-5L* (EQ-5D), is used to assess quality adjusted life years [68]. The EQ-5D consist of 5 dimensions: mobility, self-care, usual activities, pain/discomfort and anxiety/depression. Each dimension has 5 levels: no problems, slight problems, moderate problems, severe problems and extreme problems. The EQ-5D index is calculated by applying predetermined weights to the 5 dimensions, and gives a societal-based global ‘utility score’ of the participant’s health status on a scale between − 0.33 (worse than death) and 1 (perfect health). Based on these utility scores at T0 and T1, Quality-Adjusted Life Years (QALYs) were calculated for each participant with the Area Under the Curve method: ((EQ-5D T0 + EQ-5D T1)/2)*(3/12) and using the Dutch index tariff [69]. This questionnaire has been validated in IBD patients [70].

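### The societal cost list has no place for participants' own travel and unpaid time for MBCT; by itself this favours MBCT, but the net bias in the societal ICER is unknown

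*Protocol article*

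**What the plan says.** The protocol article has two sections headed Cost-effectiveness, one under Outcome measures and one under Statistical analysis.

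The one under Statistical analysis says the evaluation will be "carried out from both a healthcare and societal perspective considering direct as well as indirect costs". It then enumerates what will be costed: "We will consider three types of costs: (1) intervention costs of offering MBCT; (2) costs related to healthcare uptake". The third and last type in the list is confined to absence from work. On the source of the data it says: "Data on resource use (healthcare uptake) and productivity losses will be collected with the TiC-P".

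The one under Outcome measures describes the TiC-P more broadly, as a "reliable and valid measure of healthcare utilization and productivity losses at work and in daily life".

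The section Intervention: MBCT sets out what a participant has to do: "eight weekly 2.5 hour sessions, a six hour silent day between session 6 and 7, and daily home practice of 45 minutes". The course is held in the three cities where patients are treated. Under Comparator: treatment as usual, TAU participants are offered MBCT only after their final assessment.

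**The concern.** A societal perspective is meant to count resources whoever bears them. The list here is worded as complete, and its intervention item is the cost of offering the course, which is naturally read as the provider's cost. Travel to the sessions and the unpaid hours spent there have no line, and no instrument is described as collecting them. Apart from absenteeism, the societal analysis is therefore the healthcare analysis under another name.

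The part of this that belongs to the MBCT course falls on one arm only within the costed period. Leaving out a non-negative cost that only MBCT participants bear lowers MBCT's incremental cost in every bootstrap replicate. For this item, it raises MBCT's acceptability curve or leaves it level at every threshold. The Discussion ties implementation to whether MBCT turns out to be cost-effective, so the societal result should mean what its label says. The healthcare-perspective result and the primary HADS analysis are not touched.

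**Working it through.** The document states no cost, QALY or ICER figure for this item, so there is nothing to reproduce. The check has three steps.

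**1. Participant burden (Intervention: MBCT)**

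- Contact hours: 8 × 2.5 + 6 = 26 h.
- Attendances: 8 sessions + 1 silent day = 9.
- Home practice at 0.75 h per day, assuming 7 to 8 weeks: 0.75 × 49 = 36.75 h to 0.75 × 56 = 42 h.
- Total: 26 + 36.75 = 62.75 h to 26 + 42 = 68 h.
- TAU arm, trial MBCT within 12 months: none, since the course is offered after the final assessment.

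**2. Omitted cost per full attender**

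Cost = hours × value per hour + 9 × cost per return trip + 9 × travel hours per trip × value per hour. Every unit value below is an assumption; none is in the document.

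| Scenario | Calculation | EUR |
|---|---|---|
| A. Travel only, time not valued; EUR 3 per trip | 9 × 3 | 27 |
| B. Contact and travel time at EUR 5/h; EUR 3 and 0.5 h per trip | 26 × 5 + 9 × 3 + 9 × 0.5 × 5 | 179.50 |
| C. Contact and travel time at EUR 15/h; EUR 6 and 0.75 h per trip | 26 × 15 + 9 × 6 + 9 × 0.75 × 15 | 545.25 |
| D. As C but with home practice (68 h); EUR 10 and 1 h per trip | 68 × 15 + 9 × 10 + 9 × 1 × 15 | 1,245 |
| E. All 68 h at EUR 20/h; EUR 15 and 1 h per trip | 68 × 20 + 9 × 15 + 9 × 1 × 20 | 1,675 |

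The analysis is primarily by intention to treat, so the relevant figure is per randomised MBCT participant. As an illustration, suppose the 28% dropout used in the sample size calculation meant no attendance at all. Each figure is then multiplied by 0.72: A becomes about EUR 19, C about EUR 393, E about EUR 1,206. Partial attendance by the others would lower them further.

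**3. Shift in the ICER from this item alone**

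Shift = omitted cost ÷ incremental QALYs, here for a full attender and an assumed positive gain.

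| Scenario | Gain 0.02 QALY | Gain 0.05 QALY |
|---|---|---|
| A | 27 / 0.02 = 1,350 | 27 / 0.05 = 540 |
| B | 8,975 | 3,590 |
| C | about 27,260 | 10,905 |
| D | 62,250 | 24,900 |
| E | 83,750 | 33,500 |

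The sign of this item does not depend on the assumptions. Its size depends on them almost entirely: E is about 62 times A (1,675 / 27).

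**What else the list leaves out.** Set against the description of the TiC-P under Outcome measures, the list keeps absenteeism but not other losses at work or losses in daily life. It also has no line for patients' travel and time for ordinary care, in either arm. If MBCT improves functioning or reduces care visits, leaving these out works against MBCT.

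**The case against.** A reader might infer that the societal ICER as a whole is biased in favour of MBCT. The document does not support that. The list has other gaps, and the productivity ones could run the other way if MBCT helps distress, fatigue and sleep. TAU may include other psychosocial treatment, which also costs patients travel and time. Only the part attached to the MBCT course is one-sided; the wider category of patient travel and time is not.

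Three further objections also have force.

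- Participants' time is not wholly uncounted. Paid hours missed for a session may enter through absenteeism. What remains is travel and unpaid time.
- Whether to value leisure time, and above all home practice, is a methodological choice to which the document does not commit the trial.
- The euro figures are assumed, and those in the tables describe someone who attends everything.

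The remaining objection is that this is a condensed article and that the cited costing guideline and the full protocol are not shown. That bars any claim about what those documents contain. It does not remove the point, because the article does not simply leave the cost components open. It names three types under a declared societal perspective, and followed as written that rule excludes participants' travel and unpaid time.

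**Conclusion.** The point holds in a limited form. The cost list is narrower than the declared perspective, and participants' travel and unpaid time for MBCT (9 attendances, 26 contact hours) are outside it. That omission, taken alone, understates MBCT's incremental societal cost. Under the assumed unit values the amount is about EUR 27 to about EUR 1,700 per full attender, and less per randomised participant when attendance is incomplete. The upper end includes home practice, which is the most debatable component.

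The net direction and size of bias in the societal ICER cannot be determined from the document. The matter is worth correcting because the societal label claims more than the list delivers. It bears on one of two perspectives in a secondary evaluation.

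**What to change.** In the societal analysis only:

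- Add a cost type for participants' travel and attendance time for MBCT. Use session attendance, which the per-protocol definition already requires. Apply a standard travel cost per trip by centre or course city: individual distance is not among the characteristics listed as collected, and contact details are held separately. Take values from the costing manual already cited.
- Report the result with and without a value on unpaid time.
- Use a sensitivity analysis for overlap with absenteeism, since nothing shows that the reason for an absence is recorded.
- Confine home practice to a sensitivity analysis. The MAQ can supply it: "The first 2 items measure formal practice in terms of frequency and average duration of practice".
- Reconcile the productivity items with the description of the TiC-P under Outcome measures: either cost the at-work and daily-life losses or say why they are left out.

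If this is not wanted, label the result healthcare plus absenteeism (a restricted societal perspective) and limit the conclusion to that. Relabelling needs no data.

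The cost is a few lines in the economic analysis plan and a little derivation work. With standard trip costs it should need no new data collection, which matters because recruitment closed in September 2022. The drawback for the sponsor is that, for this item, the societal ICER becomes less favourable to MBCT.

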#### Treatment effects at post-treatment: primary outcome

All analyses will be performed and reported according to the CONSORT guidelines, i.e. primarily on intention-to-treat basis. Treatment effects on the primary outcome (psychological distress at post-treatment, assessed with the HADS) will be analysed using Linear Mixed Effect models, with time, group (MBCT + TAU versus TAU) and Group*Time interaction effects added as fixed effects, while controlling for baseline HADS score and stratification variables (i.e. centre, sex, IBD type). To account for possible dependency caused by clustering in intervention groups, we will add ‘group’ as a random effect if the intra-cluster correlation ≥ 0.05. Restricted maximum likelihood will be used as estimation method to handle missing data. Effect sizes will be calculated using Cohen’s *d*, with values of 0.20–0.50 indicating small effects, 0.50–0.80 moderate effects, and > 0.80 large effects [73]. Cohen’s *d* will be calculated by dividing the adjusted group difference between the means at T1 by the pooled standard deviation at T0.

We will also perform a per-protocol analysis selecting all participants who completed at least half of the MBCT sessions (4 or more) for those assigned to the MBCT condition and inversely, all who have not participated in any mindfulness intervention for those assigned to the TAU condition.

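### The economic analysis names no baseline or stratification adjustment for incremental QALYs; regression on baseline EQ-5D utility would be a nearly free gain in precision

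*Protocol article*

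**What the plan says.** The Cost-effectiveness section under Statistical analysis sets out the evaluation step by step.

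- QALYs: "Health related QoL data (based on EQ-5D) from baseline up till 12 months will be used to calculate QALYs using the trapezium rule".
- Comparison: "Overall mean and median costs and health related QoL will be compared across the conditions". Interval estimates are planned only for the contrasts judged relevant.
- Summary: "Incremental cost-effectiveness will be determined in terms of incremental costs per QALY gained", and "The Incremental cost-effectiveness ratio will be determined on the basis of incremental costs and effects of MBCT compared to TAU".
- Uncertainty: "Bootstrap simulations with 1.000 replications will be used to get uncertainty intervals in our economic evaluation", followed by an acceptability curve and multiple imputation for missing data.

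No covariate is named in any of these steps. The primary model, by contrast, is fitted "while controlling for baseline HADS score" and the stratification variables (centre, sex, IBD type). The secondary-outcome and follow-up models carry the same kind of adjustment. EQ-5D and TiC-P are not on the list of secondary outcomes, so that adjustment does not extend to them.

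The Cost-effectiveness section under Outcome measures gives another QALY definition: "Based on these utility scores at T0 and T1, Quality-Adjusted Life Years (QALYs) were calculated for each participant", multiplied by 3/12 of a year.

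**The concern.** A trapezium-rule QALY is partly made of the baseline measurement, and baseline utility also predicts the later utilities. If the arms differ at T0 by chance, a crude QALY difference carries part of that gap, which has nothing to do with MBCT. Randomisation is stratified by hospital, sex and IBD type, none of which balances utility directly.

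What is at stake is the precision of the ICER and the acceptability curve. The Discussion links implementation of MBCT to whether it proves cost-effective, so avoidable noise in the incremental QALY matters. Baseline EQ-5D is already collected from every participant.

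**Working it through.** The article gives no precision or sample-size figure for the economic evaluation, so there is no stated figure to reproduce.

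**Inputs from the article.** Five EQ-5D visits (0, 3, 6, 9, 12 months); trapezium rule; 68 per arm (Sample size calculation).

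**Inputs assumed.** Utility SD 0.20 at each visit, correlation ρ between visits of 0.5 to 0.7, and complete data. The percentage reductions depend on ρ only, not on the SD or the sample size.

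**Weights.** Over 12 months the QALY is (U0 + 2U1 + 2U2 + 2U3 + U4)/8, so baseline utility has weight 0.125.

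**Formulas.** Let v = Var(QALY)/SD² and c = Cov(QALY, U0)/SD². The squared correlation r² = c²/v is the fraction of variance that adjustment removes. The SE of the difference is SD·√(2v/68) without adjustment and that value times √(1 − r²) with it. The SE of a chance baseline difference is 0.20·√(2/68) = 0.034, and a one-SE imbalance shifts the crude QALY difference by c × 0.034 on average.

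*Exchangeable (same correlation between all visits):* v = 0.21875 + 0.78125ρ; c = 0.125 + 0.875ρ.

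*Decaying, AR(1) (ρ between adjacent visits):* v = 0.21875 + 0.375ρ + 0.25ρ² + 0.125ρ³ + 0.03125ρ⁴; c = 0.125 + 0.25(ρ + ρ² + ρ³) + 0.125ρ⁴.

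| Structure | ρ | v | c | r² | SE crude | SE adjusted | Shift per one-SE imbalance |
|---|---|---|---|---|---|---|---|
| AR(1) | 0.5 | 0.486 | 0.352 | 25% | 0.024 | 0.021 | 0.012 |
| AR(1) | 0.7 | 0.654 | 0.538 | 44% | 0.028 | 0.021 | 0.018 |
| Exchangeable | 0.5 | 0.609 | 0.563 | 52% | 0.027 | 0.019 | 0.019 |
| Exchangeable | 0.7 | 0.766 | 0.738 | 71% | 0.030 | 0.016 | 0.025 |

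**Sensitivity.** At ρ = 0.3 the reduction is 15% (AR(1)) or 33% (exchangeable). SEs and shifts scale in proportion to the SD: at SD 0.10 they halve. With 49 per arm (the 98 that the article requires before its dropout allowance), every SE grows by √(68/49) = 1.18.

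**Three-month formula.** With QALY = ((U0 + U1)/2) × 3/12, baseline is half of the area. Then r² = (1 + ρ)/2, which is 75% at ρ = 0.5 and 85% at ρ = 0.7.

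**Costs.** The fraction removed is again the squared correlation of baseline with follow-up costs. An assumed correlation of 0.2 to 0.6 gives 0.2² = 4% to 0.6² = 36%. Baseline recall is four weeks against three months at each later visit, which makes baseline cost a noisier covariate.

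**The case against.** A reader might infer that the plan has decided against adjustment. The text does not say so. It never calls the differences unadjusted, and its words on incremental costs and effects are compatible with regression-adjusted increments. The article condenses version 5 of a research protocol that is not shown, and covariates of an economic model are often left to such a document. This stands: the point is not a stated error. It remains worth raising because the section otherwise specifies each step, and following it as written leads to a crude comparison.

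A reader might also infer that the ICER would be biased. It would not be. Under randomisation the crude difference is unbiased, and chance imbalance is already part of its standard error and of the bootstrap distribution. The shifts in the table are therefore not an error on top of the SE; they show how much of the SE is avoidable.

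It is also fair that the magnitudes rest on an SD and correlations absent from the article. Equal correlation between all visits favours adjustment, because it lets baseline predict month 12 as well as month 3. The AR(1) rows are given for that reason.

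The case for adjusting costs is weaker and should not be given the same weight as the case for QALYs.

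**Conclusion.** The point holds as an improvement in precision, not as a flaw that invalidates the evaluation. As described, the economic comparison gives a valid but less precise QALY difference than the data allow. For the 12-month QALY and correlations of 0.5 to 0.7, baseline adjustment removes about 25-44% of the variance under decaying correlation and 52-71% under exchangeable correlation. The gain is smaller if correlations are lower, and larger if the three-month definition is the one used. The cost side is optional.

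Separately, the two Cost-effectiveness sections contradict each other on the QALY horizon. This is in the text itself and does not depend on any assumption.

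**What to change.** 1. State that incremental QALYs are estimated by regression on arm, baseline EQ-5D utility and the stratification factors (centre, sex, IBD type).
2. Estimate incremental costs by regression on arm and the same factors. Adding baseline TiC-P costs is optional; if they are used, say so in advance.
3. Refit both models on the same resample in each of the 1,000 bootstrap replicates, so that the correlation between costs and QALYs is kept. Build the ICER and acceptability curve from these adjusted estimates.
4. Reconcile the QALY definition under Outcome measures (T0 and T1 over three months) with the one under Statistical analysis (baseline to 12 months).

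The cost is a short text change and a few lines of code, with no new data. Fixing it before the economic results are seen also removes a later choice between adjusted and crude ICERs.
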